## Abstract

**Background:**

The Aotearoa/New Zealand population is ageing and numerous studies demonstrate with this phenomenon comes increases in non-communicable diseases, injuries and healthcare costs among other issues. Further, significant inequities exist between Māori (Indigenous peoples of Aotearoa/New Zealand) and non-Māori around poor ageing and health. Most research addressing these issues is deficit oriented; however, the current research project takes a strengths-based approach that highlights the potential of kaumātua (elders) by asserting mana motuhake (autonomy, identity and self-actualisation). We believe that the esteem of elders in Māori culture signals transformative potential. Specifically, this project utilises a ‘tuakana-teina’ (older sibling/younger sibling) peer-educator model, where kaumātua work with other kaumātua in relation to health and wellbeing. The objectives of the project are (a) to develop the capacity of kaumātua as peer educators, whilst having positive impacts on their sense of purpose, health and wellbeing; and (b) to enhance the social and health outcomes for kaumātua receiving the intervention.

**Methods:**

The research is grounded in principles of Kaupapa Māori and community-based participatory research, and brings together an Indigenous community of kaumātua, community health researchers, and academic researchers working with two advisory boards. The project intervention involves an orientation programme for tuakana peer educators for other kaumātua (teina). The research design is a pre- and post-test, clustered staggered design. All participants will complete a baseline assessment of health and wellbeing consistent with Māori worldviews (i.e., holistic model). The tuakana and teina participants will be divided into two groups with the first group completing the intervention during the first half of the project and the second group during the second half of the project. All participants will complete post-test assessments following both interventions allowing comparison of the two groups along with repeated measures over time.

**Discussion:**

The findings will provide an evidence base for the importance and relevancy of kaumātua knowledge to create contextually based and culturally safe age-friendly environments that facilitate engagement and participation by kaumātua for kaumātua. If the model is effective, we will seek to facilitate the dissemination and scalability of the intervention.

**Trial registration:**

Australia New Zealand Clinical Trial Registry (ACTRN12617001396314); Date Registered: 3 October 2017 (retrospectively registered).

**Electronic supplementary material:**

The online version of this article (10.1186/s12877-019-1041-2) contains supplementary material, which is available to authorized users.

## Background

The Aotearoa/New Zealand (hereafter referred to as ‘Aotearoa’) population is ageing and numerous studies demonstrate with this advancing age comes increases in non-communicable diseases, injuries and healthcare costs among other issues [1]. Accordingly, there is a general assumption that the increasing percentage of older people over the first half of the twenty-first century will lead to an increasing burden on the socio-economic system [1]. Further, significant inequities exist between Māori (Indigenous people of Aotearoa) and non-Māori around poor ageing and health outcomes [2–4], that, in turn implicate individual, economic, social and cultural costs [2–4]. This assumption has been central to public discourses surrounding Aotearoa’s ageing population and is underpinned by a deficit model emphasising limitations, weakness, and dependency [2]. Certainly ageing is associated with increased disease rates and costs, yet there are also many positive elements of ageing. Thus, the central discourse surrounding the ageing population needs to shift if Aotearoa is to re-frame older people as highly valuable assets to society. The current research project takes a strengths-based approach that highlights the potential of kaumātua (elders). We believe that the esteem of elders in Māori culture in principle (if not always in practice) signals transformative potential. Our approach is part of the Ageing Well National Science Challenge in Aotearoa (https://www.ageingwellchallenge.co.nz/), which looks to provide more focus on positive ageing as part of the government’s strategic approach to science investment.

Consequently, the present research emphasises the strengths-based approach as grounded in an Indigenous philosophy within a culture that is often overlooked in relation to how it can influence New Zealand’s national culture in general and provide innovations in socio-economic spaces. Māori culture venerates its elderly, such is its centrality to a Māori way of life; from the way that typical Māori whānau (extended family) operate beyond the bounds of the traditional western family model to tikanga (customs and protocols) on the marae (community meeting space) and in various community settings [5, 6]. As Sir Hirini Moko Mead states: “The kaumātua and kuia, the elders, are often the guardians of tikanga. They are expected to know” and “Experience is definitely helpful in knowing what to do [6] (p. 14).” Mead also noted that kaumātua have active roles in the community including governance and mediating disputes. Further, kaumātua are often the glue that hold fragmented extended families together through raising grandchildren [7].

Nonetheless, Māori, like all other people, face significant transition points as they age, such as loss of independent living (e.g., loss of driver’s license), loss of a spouse, and changing health conditions [1, 8, 9]. Successfully navigating these transitions depends on being able to manage emotional and socio-economic factors, as well as service systems, whilst often being reliant on family or whānau [10–14]. Kaumātua who are unable to successfully navigate significant transition points during ageing are exposed to many negative consequences including poor quality of life, social isolation, and poor health outcomes [15, 16]. These transitions for kaumātua are substantial and different than in other ageing populations given the context of significant health and social inequities. Thus, these transitions need to be addressed directly to facilitate positive ageing.

### Kaumātua Mana Motuhake

Mana motuhake is a concept that foregrounds independence and autonomy to achieve actualisation—including collective determination and independence. In this manner, kaumātua assert their independence and autonomy so they can live a life of longevity and quality for self and others [17]. Historically, kaumātua have faced a dominant society that has failed to realise their full potential as they age [18]. Yet, for Māori, the elderly are “carriers of culture, anchors for families, models for lifestyle, bridges to the future, guardians of heritage, and role models for younger generations [19] (p. 14).” The current project is invested in upholding tino rangatiratanga (independence and autonomy) and mana (status and prestige as viewed by self and others) via a culturally appropriate *‘*tuakana-teina’ peer-educator model where kaumātua work with other kaumātua in relation to significant life-transitions [17]. Accordingly, this research values older people in all settings and views their experience and status as key tools for positive ageing. Further, this research is grounded in Māori epistemologies surrounding ageing [20] and provides insights into how a Māori worldview of ageing and Māori practices surrounding ageing have the potential to improve life courses for all New Zealanders.

Whilst the research is grounded in a strengths-based approach, it does not assume that the tikanga surrounding Māori elders described above is consistent or practiced by all Māori. Rather the research imbibes cultural concepts into a peer-educator/peer-support model to help shift practices in working with elders to address significant life-transitions and to ideally help change the dominant public discourse surrounding ageing. The research includes Māori epistemology and worldviews in a way that is accessible to all (e.g., including materials in both English and Māori languages). Thus, the ageing population is valued and has mana motuhake—that is, self-determination as their life-situations evolve including the responsibility of taking on new and vital roles.

### Tuakana/Teina peer-educator/peer-support model

The research extends existing understandings related to the improvement of outcomes for kaumātua by focusing on the possibilities of using elders as peer educators via the Indigenous concepts of tuakana-teina. Tuakana-teina is a Māori customary concept [6] signifying the importance of the relationship between an elder and younger sibling, or cousin, of the same sex; however, it can also be based on experience and training and hence why it was chosen for this project. The concept is based on responsibility and reciprocity, and can be pedagogically applied in peer-education mentor/mentee settings [21]. The tuakana-teina peer-education pedagogy in the present research aligns with this central philosophy, where the reciprocal relationship is underpinned by self-efficacy and responsibility. The tuakana role includes culturally resonant values, principles, and practices determined by the spiritual balance between tapu (sacred) and noa (ordinary); the exercise of mana, pono (truth, integrity, faithfulness), aroha (love, compassion, mercy, empathy) and tika (correctness, justice, fairness). Pono concerns the ethics of how tapu is addressed and mana is exercised [6, 22].

With the ultimate goal of promoting a self-determined life and improving health and social outcomes, this peer-education approach essentially encourages self-efficacy and mana for both the tuakana and the teina, whilst profiting social integration and engagement. More practically, both parties are not only able to socially interact with each other, the teina receives valued support that may prevent social isolation as kaumātua work through life-events, whilst the tuakana is given further meaning and engagement via the self-efficacy that supporting another can enable. Inherently, the peer-education model develops age-friendly social environments that value knowledge and cultural concepts such as whakawhanaungatanga (making social connections), tautoko (advocacy, support) and mātauranga (Indigenous knowledge) [5, 6, 21].

Drawing on well-known theories including social learning theory [23], theory of reasoned action [24], and diffusion of innovation theory [25], the research literature demonstrates that peer education/support is an effective method of enhancing a variety of health, social, and economic conditions [26–29]. Peer support and education include a range of assistance activities provided by lay individuals (non-professionals) to others experiencing a health or social need who are members of the same age, health, culture, ethnicity, or other cohort [30]. Peer support is different from everyday whānau and community support networks where people help each other because of existing relationships. It is also different from organisation-driven, “para-professional” support—even though such programmes may use peer supporters. Peer education/support utilises lay individuals and relies on a created social network based on shared health or social service needs. Such networks are commonly created by health professionals and social service agencies but may include self-help groups [30].

Peer education/support is used to help people manage various ‘age and stage’ life-transitions, including acute and chronic situational health and social stressors [30]. Peer educators are mostly used with younger populations, but elder peer educators have recently featured in self-management of chronic conditions [31], raising awareness of health [32, 33], physical activity and fall-prevention in older age [34–37], successful ageing [38], and palliative care [39–41]. In addition to improving health outcomes of recipients, peer education/support has also shown positive outcomes for peer educators’ own sense of wellbeing and maintenance of health self-management and programme engagement [42–44].

### Research aims

We seek to address the mana motuhake of kaumātua, asking: What are the outcomes of a ‘tuakana-teina’ peer-educator model, where kaumātua work with other kaumātua in relation to wellness, social integration/connectedness, engagement, life-enhancement, independence, and, in particular, significant life-transitions? The project has four specific objectives: (a) To develop the capacity of kaumātua as peer educators/supporters and have positive impacts on their sense of purpose and health and wellbeing; (b) To enhance the social and health outcomes for kaumātua receiving the intervention; (c) To determine the cost-effectiveness of the intervention; and (d) To determine whether and how the intervention could be scalable through effective dissemination and implementation processes.

## Methods

### Methodology

The project is guided by Kaupapa Māori [45, 46] and a community-based participatory research approach (CBPR) [47, 48]. Kaupapa Māori and CBPR are collaborative research processes that underpin every phase of the research process. In New Zealand considerable advances have been made in working with mātauranga, science and other disciplines to develop innovative methods that are non-exploitative of Māori communities, that work with their strengths rather than deficits and that lead to advancement of mutually beneficial knowledge and applications. These two approaches emphasise this mission and ensure that the project is kaumātua and end-user led. With their wealth of life experience and mātauranga, kaumātua are strongly placed to extend their existing significant cultural roles to include the spread of knowledge needed to empower other kaumātua and their whānau in life-transitions. The Kaupapa Māori approach here centralises the mana motuhake of kaumātua as having value and at the same time responsibility [49].

In the last 30 years, Kaupapa Māori has emerged as a key discourse theory and praxis [46] and, in the context of the present research, provides a culturally appropriate methodology as it normalises Māori worldviews and practises [50]. Indigenous academics, theorists, activists, and researchers agree that Kaupapa Māori is an approach that focuses on self-determination and local context by prioritizing Indigenous aspirations and history [46, 51]. The key concepts of this approach are the validity of a Māori epistemology; the legitimacy of the rights of Māori as Indigenous peoples [51] and the importance of tikanga and mātauranga [45, 46]. Mātauranga Māori is the knowledge that underpins a Māori epistemology and provides the basis of technological and philosophical skills of the community; it is a by Māori for Māori approach to research [52, 53].

CBPR is a collaborative research approach that equitably involves academic and community partners in the research process and recognises the unique strengths that each partner brings [47]. Following the practice of many CBPR partnerships and Kaupapa Māori principles [46, 47], we use two advisory boards to guide our work: (a) a Board Advisory Group; and (b) an Expert Advisory Group. The Board Advisory Group is comprised of trustees of Rauawaawa Kaumātua Charitable Trust (RKCT; an organisation that serves the health and social wellbeing needs of elders using a Māori philosophy) who are all kaumātua themselves. This was fundamental to the methodology because of the centrality of representatives of the research participants to the decision-making process of the project. It provides oversight, guidance and input into all the research methods, procedures, data-collection processes, and analysis that the research team is conducting in this project. The Expert Advisory Group includes experts in health and social issues related to the project. It ensures the intervention and research design aligns with best practices in ageing transitions. We meet with these groups bi-monthly during the development of the research design and intervention and quarterly through the duration of the project.

Our research team involves an ongoing research partnership between a community organisation (i.e., RKCT), and academics from multiple disciplines from the University of Waikato including communication, public health, economics, and Māori and Indigenous Studies. We underwent training during the first month of the project on cultural safety, research protocols and ethics, CBPR and Kaupapa Māori principles to support our research methodology and ensure all researchers were clear about expectations.

### Intervention development

We will develop a “Tuakana-teina/peer education orientation programme” for life-transitions of kaumātua. The programme is framed as an ‘orientation’ instead of a training programme to reinforce the research project’s participant driven nature, whilst at the same time making it clear that the project itself will draw on the extant knowledge and expertise of kaumātua themselves. This programme development will be informed by knowledge generated from our previous research projects and other related research about culturally relevant protocols and processes during life-transitions for kaumātua. Consultation and interaction with tuakana (peer supporters) will inform the development and delivery of the orientation material. Teina (peers learners) also will have input into the effectiveness of the intervention’s implementation, and areas of strength and weakness in the processes used.

Our own research and RKCT’s service providers identified key challenges, barriers, and opportunities related to the life-transitions as part of the proposal writing. Together these provided a solid foundation for the orientation programme. Although we investigated other research [41, 54, 55], the primary concern will be to develop a Māori model of peer support for use with kaumātua. As part of the proposal writing, we conducted a literature review of critical cultural perspectives and values, including Te Ao Māori (worldview); mātāpono (principles) and tikanga; kaumātua roles; tuakana and teina as roles and concepts; and Māori approaches to communication. In addition, we reviewed peer support as it is discussed in Māori and Indigenous contexts, as well as the ageing, education, and health literature.

The development of the intervention will include extensive consultation with kaumātua, the Board Advisory Group, and Expert Advisory Group to ensure that tikanga and Māori communication approaches remain central. We will keep minutes of all advisory group meetings, meetings of the team that developed the Tuakana Orientation Programme, and consultation sessions with kaumātua. These practices will ensure the integrity of the development process. We will run a full, three-session pilot programme with kaumātua from a different region and organisation. This pilot will inform the final design of the Tuakana Orientation Programme; we will create a manual for the intervention that includes instruction for orientation, implementation and evaluation.

### Orientation Programme process

The orientation of the tuakana will be completed at two time periods for Tuatahi (first group, T1) and Tuarua (second/comparison group, T2); these will correspond to when each group commences the intervention with teina. Orientation activities will be run by members of the research team with support from the Board Advisory Group. The orientation will include sharing of: (a) Māori values and mātāpono; (b) definitions of tuakana-teina/peer support; (c) four kinds of support; (d) forms of Māori communication; and (e) specific communication tools to support the tuakana in their conversations with teina. The final program will be comprised of four 4-h sessions over two weeks. Each session includes breaks for morning tea and lunch. The initial sessions focus on exploration of the programme, with the later sessions focusing on the tuakana-teina relationship, skill development, and communication practice. “Booster sessions” will be offered to follow-up on the information and to provide additional opportunities to practice the skills.

### Study design

The research design for the evaluation of the orientation programme is a pre- and post-test, clustered staggered design with T1 (target *n* = 15) and T2 (target *n* = 15) groups. T1 will participate in the orientation programme initially, while T2 will participate in a subsequent orientation. The peer educator capacity of tuakana will be assessed at three stages: pre-intervention, post-intervention for the T1 group, and post-intervention of the T2 group. After the orientation programme, each tuakana will talk with each teina at least three times to address the specific life-transitions of teina. Teina also will complete three evaluations with variations for the two groups: (a) T1: pre-intervention, approximately four months post-intervention, and then four months after the second evaluation; (b) T2: pre-intervention, approximately four months after initial survey, and then four months post-intervention. This staggered approach was approved by the Board Advisory Group during the original proposal as fitting the mission of the organisation and the needs of kaumātua. Consistent with Kaupapa Māori principles, withholding an intervention from participants is not ethical. Thus, the research design enables a rigorous comparison of the orientation programme whilst ensuring that all teina receive the intervention. Further, the use of a staggered design is a strong, and pragmatic design for interventions in the health service sector [56]. Figure 1 illustrates the staggered research design. The project is registered with the Australia New Zealand Clinical Trial Registry (ACTRN12617001396314).

**Fig. 1 Fig1:**
[figure not shown]
Study Design

### Sample and recruitment

Tuakana will be purposively sampled to include kaumātua with effective peer educator attributes. The advisory groups considered the relevant peer educator attributes for ageing research [41] and attributes within Te Ao Māori such as mana, pono, aroha and tika [6, 19]. Tuakana will receive koha (an offering) towards their participation in the programme, conversations with teina, and data collection over the duration of the project (approximately $45/event).

The project will have a target of 180 teina participants randomly selected from the RKCT client base of approximately 600 kaumātua that affiliate to various iwi (tribes). Tuakana will be removed from the sampling frame. Teina will be assigned to a tuakana with matched biological sex. The only exclusion criteria is ethnicity (i.e., not being Māori). Decline and retention rates (including reasons such as withdrawal and passing away) will be tracked. Teina will receive koha as a contribution towards their participation in conversations and data collection (approximately $40/event). Tuakana and teina will be assigned to T1 and T2 groups ideally using random assignment although convenience assignment will be accommodated and tracked (e.g., when they were able to participate or to match tuakana/teina).

The sample sizes of tuakana and teina were determined by a balance of resources and statistical power to determine the optimal design. We conducted power and sample size estimates based on the research design [57] and confirmed with the ‘od.exe’ software package [58]. The following assumptions were made: (a) probability value = .05; and (b) rho (intra-class correlation) = .10. Six teina for each tuakana results in power of .80 with a medium effect size (d = .55). A medium effect size was chosen given prior research on the impact of elder peer educators on self-rated health and related wellbeing outcomes [37, 38].

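### Same-sex pairing is allowed to override random assignment to T1/T2, an avoidable reason to depart from randomisation

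*Protocol article*

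**What the plan says.** All the rules are in the protocol article, under Sample and recruitment unless noted.

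- Tuakana: "Tuakana will be purposively sampled to include kaumātua with effective peer educator attributes". Sex is not named among the attributes.
- Teina: "The project will have a target of 180 teina participants randomly selected from the RKCT client base of approximately 600 kaumātua". Stratification by sex is neither stated nor excluded.
- Pairing: "Teina will be assigned to a tuakana with matched biological sex". No other pairing criterion is given.
- Allocation: "Tuakana and teina will be assigned to T1 and T2 groups ideally using random assignment although convenience assignment will be accommodated and tracked", with the examples "e.g., when they were able to participate or to match tuakana/teina".
- Layout (Study design): "clustered staggered design with T1 (target *n* = 15) and T2 (target *n* = 15) groups".
- Power: "Six teina for each tuakana results in power of .80 with a medium effect size (d = .55"). This is the only place where six per tuakana appears, and it agrees with 180/30 = 6.

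Study design goes on to claim that the staggered design allows a rigorous comparison.

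**The concern.** A teina can meet only a tuakana in the same group, so pairing by sex has to work within T1 and within T2. If tuakana and teina are each randomised to groups without regard to sex, the two sex mixes will often disagree within a group. The article then permits a non-random move so that pairs can be formed. Who is moved would depend on sex and on who can conveniently be moved. The T1/T2 contrast would then no longer rest on randomisation for those people. The need for such moves can be foreseen from the pairing rule and can be designed out.

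**Working it through.** **Inputs from the article.** 30 tuakana (15 + 15), 180 teina (average six each), intra-class correlation 0.10, d = 0.55, alpha 0.05 (taken as two-sided), about 600 clients with tuakana removed (600 − 30 = 570).

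**Assumption.** The sex ratio of the client base is not given. I use p = 0.50, 0.60 and 0.70 women, with the tuakana mix proportional to it (15, 18 or 21 women of 30).

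**1. The stated power.** SE = sqrt(4 × (0.10 + 0.90/6)/30) = sqrt(0.0333) = 0.183, and 0.55/0.183 = 3.01. The noncentral t with 28 df gives power 0.828. The stated 0.80 is slightly conservative.

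**2. Whole sample: can random selection and same-sex pairing coexist?** In a random draw of 180 from 570, the number of women has 95% range 79–101, 97–119 or 116–136 (SD about 5 to 5.6). Exactly six for every tuakana arises in only about 7–8% of draws. If loads may vary, everyone is paired with 5 to 7 teina per tuakana (4 to 8 at p = 0.70). The coefficient of variation (CV) of cluster size is about 0.14 and power is 0.825. So the two rules are compatible.

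**3. A badly mismatched case.** With 15 female and 15 male tuakana and 70% women among teina, loads are 126/15 = 8.4 and 54/15 = 3.6, so CV = 2.4/6 = 0.40. The design effect is 1 + ((1 + 0.40²) × 6 − 1) × 0.10 = 1.596, against 1.50 with equal loads. Power is 0.805.

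**4. Within groups, if tuakana and teina are randomised separately and without regard to sex.**
- SD of female tuakana in T1 = sqrt(15 × p(1 − p) × 15/29) = 1.39, 1.36, 1.28. Times six, this is 8.4, 8.2, 7.7 places.
- SD of women among 90 teina in T1 = sqrt(90 × p(1 − p) × 480/569) = 4.4, 4.3, 4.0.
- SD of the mismatch in one group = root of the sum of squares = 9.4, 9.2, 8.6.
- The mean absolute mismatch is about 0.798 × SD. Over two groups, 2 × 0.798 × SD = about 15.0, 14.7 and 13.8 teina without a same-sex place at six each, or 8% of 180.

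Simulation gives the same averages. The number is 18 or more in 29–34% of draws, and an exact fit in both groups occurs in about 0.3%.

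**5. With tuakana and teina assigned within sex.** The within-group mismatch goes. What remains is the chance variation of step 2, on average about 4 teina off the six-per-tuakana layout, which slightly varying loads absorb.

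**The case against.** The best counter-argument is that little here is in conflict. Six is a power input, so loads may vary. Tuakana are sampled purposively, so the team may set their sex mix to suit the client base. An article may leave stratification to the full protocol. The convenience clause concerns T1/T2 only, and such assignments will be tracked. All of this stands, and it disposes of several stronger readings:

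- A reader might infer that random selection and same-sex pairing cannot both be met. That requires exactly six per tuakana as a quota, which the article does not state.
- A reader might infer that selected teina are displaced and the random sample is lost. The clause does not govern entry to the study, and moving someone between T1 and T2 leaves the sample unchanged.
- A reader might infer that intensity of support becomes tied to sex. The article sets a minimum of three conversations for each teina, whatever the tuakana's caseload.

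Two further points stand in part. The clause speaks of matching in general, so sex as its motive is an inference, although sex is the only criterion named. And if teina simply follow their tuakana's group, the mismatch in step 4 does not arise; the article does not say that they do.

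The clause itself remains. It is an explicit rule that lets matching override randomisation, so brevity does not explain it. Tracking records the departures but does not make those assignments random.

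**Conclusion.** The concern holds in a limited form. The article accepts non-random T1/T2 assignment for the sake of pairing, and its one stated pairing criterion makes that need foreseeable and avoidable. If tuakana and teina are randomised separately without regard to sex, about 14 to 15 of 180 teina would on average lack a same-sex place at six each. That figure rests on assumed sex ratios, a proportional tuakana mix and a load of exactly six. Flexible loads would reduce the number who need to be moved, and no resulting bias can be quantified from the article. The effect on power is negligible (0.828, and 0.805 in the mismatched case examined). The cost lies in the credibility of the group comparison. This is a weakness in the allocation rule; it is not a contradiction between selection and matching.

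**What to change.** In Sample and recruitment:

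1. Randomise tuakana to T1 and T2 stratified by sex, keeping 15 per group.
2. Then do one of two things. Either randomise teina to T1 and T2 within sex, in proportion to the tuakana of that sex in each group. Or pair each teina with a same-sex tuakana first, and let the teina follow that tuakana's randomised group.
3. Delete matching of tuakana and teina as a reason for convenience assignment. The other example, availability, is a separate matter that this change does not remove.
4. Optionally, choose the tuakana sex split close to that of the client base, which keeps loads near six.

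The cost is protocol wording and allocation lists by sex, with no extra participants. The sex split must be planned before assignment, and loads will vary slightly around six.
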